#### Outcome definitions

Safety: the number of patients who reported incidence of grade ≥3 treatment-related adverse events (according to CTCAE v5.0);Feasibility: the number of patients who complete pre-op treatment and proceed to surgery;Major Pathological Response (MPR): a reduction in the proportion of surviving tumors below a clinically significant cutoff (≤10% of surviving tumors);1-year recurrence-free survival: the proportion of all patients without HCC recurrence one year after liver resection;Objective Response Rate (ORR): the percentage of patients with complete response (CR) and partial response (PR) in all patients, and the response to treatment is based on the modified Response Evaluation Criteria in Solid Tumors (RECIST 1.1);Imaging-Pathology Concordance Rate (IPCR): the proportion of all patients with consistent PVTT regression on preoperative imaging and postoperative pathological PVTT regression assessment;PVTT regression rate: the proportion of patients with PVTT regression after treatment, divided into PVTT regression rate assessed by imaging and PVTT regression rate assessed by pathology;Median overall survival (mOS): the median difference (in months) between the date of study enrollment and the date of death due to any cause. Patients still alive at the end of the study will also be treated as censored, with the last known survival date as the last survival time;Recurrence-free survival (RFS): from radical resection to the date of the first documented tumor into recurrence or death from any cause, whichever occurred first.

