**Methods:**

This open-label, single-arm, prospective, multi-center Phase I trial will enroll 20 HCC patients with PVTT who have a resectable primary tumor and no extra-hepatic metastasis. Eligible patients will be given radiotherapy, 3Gy*10 fraction, and will receive lenvatinib 8-12mg once daily and sintilimab 200mg once every three weeks. Surgical resection will be performed 6-8 weeks after radiotherapy. The primary endpoint is safety (number of patients ≥3G TRAE) and the number of patients who complete pre-op treatment and proceed to surgery. The secondary study endpoints include Major Pathological Response (MPR), 1-year tumor recurrence-free rate, Objective Response Rate (ORR), Imaging-Pathology Concordance Rate (IPCR), PVTT regression rate, Median Overall Survival (OS) and Recurrence Free Survival (RFS).

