#### Follow-up

Within one year after the operation, imaging evaluations will be performed every 3 months which including contrast-enhanced CT/MRI of the upper abdomen and plain CT of the chest. In the second year after surgery, imaging assessments will be performed every 6 months until subjects experience disease progression. After progression, survival follow-up will be performed every 6 months. Due to the small sample size of this study, if there will be a loss of follow-up in the following process, it is necessary to supplement the sample size to ensure 20 enrolled people. Clinical visit information is detailed in **Table 4**.

**Table 4 T4:** Clinical visit information diagram.

	Screening period	Neoadjuvant Therapy(RT+ Sintilimab +Lenvatinib)			Operation			All eligible patients(Non-operated patients will be counted from the day of neoadjuvant failure and surgical patients will be counted from the first postoperative day)		
		Neoadjuvant therapy week 2 (during radiotherapy)	Neoadjuvant therapy week 4(before the start of cycle 2 of sintilimab)	Neoadjuvant therapy week 7(before the start of cycle 3 of sintilimab)	Before Operation	During Operation	1 month ± 10 days after operation	3 month ± 10 days	1st year every 3 months ±10 days	From 2^nd^ year, every 6 months ± 10 days until disease progression or death
Demographics	**√**									
Past medical history	**√**									
Vp typing of PVTT	**√**							**√**		
Child-Pugh score	**√**			**√**	**√**		**√**			
ECOG score	**√**			**√**	**√**		**√**	**√**	**√**	**√**
ICGR-15	**√**				**√**					
Routine blood test	**√**	**√**	**√**	**√**	**√**		**√**	**√**	**√**	**√**
Liver and kidney function test	**√**	**√**	**√**	**√**	**√**		**√**	**√**	**√**	**√**
Thyroid function test	**√**			**√**						
ACTH test (8:00 am.)	**√**			√						
Serum cortisol test (8:00 am.)	**√**			**√**						
Troponin	**√**		**√**	**√**						
AFP、PIVKA-II	**√**				**√**		**√**	**√**	**√**	**√**
immune-related biomarkers(PD-L1、TMB)							**√**			
Immune cell typing (CD4+ T cells, CD8+ T cells)	**√**				**√**		**√**			
Abdominal image	**√**				**√**		**√**	**√**	**√**	**√**
Lung imaging	**√**				**√**			**√**	**√**	**√**
ECG	**√**				**√**					
Inclusion and exclusion criteria judgment	**√**									
Neoadjuvant therapy		**√**	**√**	**√**						
Operation						**√**				
Efficacy evaluation				**√**				**√**	**√**	**√**
Adverse event		**√**	**√**	**√**	**√**	**√**	**√**	**√**	**√**	**√**

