#### Sample size

The main study center treated 5 HCC patients with PVTT (all VP4) between 2020 and 2022. These patients underwent surgery after using the same neoadjuvant therapy as this trial. All patients achieved good efficacy, with a postoperative MPR of 60% (3/5), and manageable safety profile, supporting this trial. Based on this result, we set the end-point of effective response rate as 60%. We simulated response rates of 10%, 20%, and 30% assumed as pathological effective naturatly before intervention. The recruiting time for whole population of the patients is 24 months, and the last enrolled patient will be followed for 12 months. Two-sided Tests with 80% power is used with type I error set at 0.05, and one-Sample tests for exponential hazard rate is used to calculate sample size. The sample size calculate by PASS software 2021 version is 6, 10 and 18 for an effective response rate 10%, 20% and 30%, respectively. Based on the maximum possible effective response rate as control at baseline, we finally set it as 30% and obtained a sample size of 18 that included 11 events. The final sample size is 20 patients, allowing for a 10% loss to follow-up.

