#### Statistical analysis

This is an open-label, single-arm, phase I clinical trial and a planned 20 eligible subjects will be enrolled. Descriptive Analysis: The description of the quantitative indicator will give the median. Baseline Demographic Analysis: Descriptive analysis of baseline demographic data, and the chi-square test or survival analysis for numerical data in the experimental and control groups, depending on the data type. Analysis of evaluation indicators: Safety and feasibility, MPR rate, 1-year recurrence-free survival rate, ORR, PVTT regression rate, IPCR, ECOG score, tumor marker changes (AFP, PIVKA-II), ICG-R15 Changes, changes in liver function, etc. analysis of variance using two independent samples t-test, nonparametric test, repeated measures design according to data type. OS and RFS will use survival analysis according to data type. Safety evaluation: Adverse events will be described by the number and incidence, and detailed descriptions of the specific manifestations and degrees of all adverse events and their relationship with the drugs used. Since it is an exploratory study, the research data and results are subject to the investigator’s evaluation, and a Data Monitoring Committee (DMC) is not specially established.

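### The 1-year recurrence-free survival endpoint does not count death as a failure, unlike RFS in the same list, and its denominator does not fit its clock

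*Protocol article*

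**What the plan says.** The Outcome definitions section of the protocol article gives two endpoints with nearly the same name. The 1-year recurrence-free survival is "the proportion of all patients without HCC recurrence one year after liver resection". RFS runs "from radical resection to the date of the first documented tumor into recurrence or death from any cause, whichever occurred first".

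The name of the 1-year endpoint varies. The Abstract calls it the "1-year tumor recurrence-free rate". The Statistical analysis section calls it the "1-year recurrence-free survival rate" and places it in a list of indicators to be compared by t-tests, nonparametric tests or repeated-measures methods. That section reserves survival analysis for OS and RFS. The Anticipated results section lists the 1-year endpoint and RFS as separate secondary endpoints.

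The plan foresees that some patients will not be resected. Feasibility, part of the primary endpoint, is "the number of patients who complete pre-op treatment and proceed to surgery". Table 4 in the Follow-up section gives such patients their own starting point for visits: "Non-operated patients will be counted from the day of neoadjuvant failure and surgical patients will be counted from the first postoperative day".

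**The concern.** Three features of the 1-year definition do not fit together.

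- **Event.** Only recurrence is a failure. A patient who dies within the year without recurrence, for example from a surgical complication, fails RFS but satisfies the 1-year definition, even though that definition also carries the word survival.
- **Denominator.** The proportion is taken over all patients, but the time point is measured from resection. A patient who is never resected has no such time point. The text does not say whether that patient is a success, a failure or excluded.
- **Name and method.** Because the 1-year rate is listed apart from the endpoints given survival analysis, it cannot be assumed to be a reading from the RFS curve. Two different one-year figures could be reported from the same patients.

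The Anticipated results section says the outcomes will be used to set the sample size of the following study. A 1-year rate that ignores deaths, or whose population is unclear, could pass into that study's assumptions.

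**Working it through.** **The plan's own figure.** The document states no target or expected value for the 1-year endpoint. Its only related figure is the sample size: 18 patients with 11 events, raised to 20. This reproduces with a one-sample exponential test if 60% and 30% are read as 12-month event-free proportions:

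- Hazards per year: −ln(0.60) = 0.511 and −ln(0.30) = 1.204.
- Events: ((1.960 + 0.842)/ln(0.511/1.204))² = 10.68, rounded up to 11.
- Probability of an event with 2 years' accrual and 1 year's follow-up: 1 − (e^(−0.511) − e^(−1.533))/(2 × 0.511) = 0.624.
- Patients: 10.68/0.624 = 17.11, rounded up to 18; 18/0.9 = 20.

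The plan presents those percentages as pathological response rates, so the link to a 1-year event-free rate is an inference. The point below does not depend on it, and the repair does not change the sample size.

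**Notation.** N = 20 enrolled (Sample size section); k resected; r recurrences and d deaths without recurrence within one year of resection. The documents give no values for k, r or d, so those used here are assumptions. Everyone resected is taken as followed for 12 months, so the Kaplan-Meier estimate equals the simple proportion.

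**All patients resected (k = N).**

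- 1-year definition as written: (N − r)/N.
- RFS at 12 months: (N − r − d)/N.
- Difference: d/N = 1/20 = 5 percentage points per death without recurrence, whatever r is.

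**Some patients not resected (k < N).** The written definition allows three readings, shown beside RFS and an all-enrolled proportion in which death and non-resection both fail. With r = 8:

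| k | d | Never-resected are successes, (N−r)/N | Never-resected excluded, (k−r)/k | Never-resected are failures, (k−r)/N | RFS, (k−r−d)/k | All enrolled, (k−r−d)/N |
|---|---|---|---|---|---|---|
| 20 | 0 | 60% | 60% | 60% | 60% | 60% |
| 20 | 1 | 60% | 60% | 60% | 55% | 55% |
| 20 | 2 | 60% | 60% | 60% | 50% | 50% |
| 20 | 3 | 60% | 60% | 60% | 45% | 45% |
| 18 | 0 | 60% | 55.6% | 50% | 55.6% | 50% |
| 18 | 2 | 60% | 55.6% | 50% | 44.4% | 40% |
| 16 | 0 | 60% | 50% | 40% | 50% | 40% |
| 16 | 2 | 60% | 50% | 40% | 37.5% | 30% |

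The first three percentage columns do not change with d: under every reading, deaths without recurrence leave the 1-year figure where it was. Non-resection can move the figure either way. With k = 16 and d = 0, scoring the never-resected as failures gives 40%, below the RFS of 50%.

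**Is k = 16 plausible?** The Discussion cites a perioperative nivolumab study with or without ipilimumab in which 21 of 27 evaluable patients had planned surgery (78%). It also cites a cabozantinib plus nivolumab study with margin-negative resection in 12 of 15 (80%). Sixteen of 20 is 80%. Those are different regimens and populations, so this shows only that the value is not far-fetched.

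**The case against.** The best defence is that the Abstract's name shows the intention: a recurrence-only rate, reported beside RFS as a separate endpoint. The fault would then be one of labelling, and the two figures agree if everyone is resected and nobody dies without recurrence. This is fair, but under that intention the survival label used elsewhere is wrong and the denominator still does not fit the clock. The text needs repair either way.

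It can also be said that deaths and non-resection are not hidden. Feasibility and grade 3 or higher treatment-related events are primary, and both RFS and all-cause OS are reported. That stands, and it limits the severity. How censored patients are handled may properly be left to an analysis plan that is not shown. The definition of the event may not, because this document states it in two incompatible ways.

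Two stronger readings are tempting and should not be drawn.

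- A reader might infer that never-resected patients count as successes, so that failure to reach surgery inflates the rate. The text never says so, and a patient without a resection has no one-year point at which to be scored. They could be successes, failures or excluded; the rule is missing.
- A reader might infer from "the last enrolled patient will be followed for 12 months", with surgery 8 to 10 weeks after treatment starts (2 weeks of radiotherapy plus 6 to 8 weeks), that the last patients have only about 9.7 to 10.2 postoperative months. That phrase is an input to the sample size calculation, and no data cut-off is stated. The Follow-up section and Table 4 schedule imaging from the operation through the first year and into the second.

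**Conclusion.** The concern holds for the event and the denominator. As written, the 1-year endpoint treats death without recurrence as a success while RFS in the same list treats it as an event. The excess over 12-month RFS is 5 percentage points per such death if all 20 patients are resected. When some are not resected, the figure is ambiguous in size and direction, because no rule covers them. In the assumed case of 16 resected, 8 recurrences and 2 deaths, the readings run from 40% to 60% against an RFS of 37.5%.

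The 5-point figure rests only on N = 20, complete resection and complete one-year follow-up. The other percentages rest on assumed counts and illustrate the spread; they are not forecasts. Neither inflation by non-resection nor inadequate follow-up is established by the document.

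Severity is moderate. The endpoint is one of seven secondary endpoints in an exploratory single-arm trial and no decision rule is attached to it, but it is among the outcomes meant to inform the size of the next study.

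**What to change.** Define the 1-year rate as the 12-month Kaplan-Meier estimate of RFS as already defined: recurrence or death from any cause, counted from radical resection, in resected patients. Use one name for it in the Abstract, Statistical analysis, Outcome definitions and Anticipated results sections, and move it to the survival-analysed endpoints.

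If a proportion over all enrolled patients is also wanted, state that death and failure to reach resection both count as failures. A separate event-free survival endpoint from enrolment is optional and is not needed to resolve the contradiction.

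If a recurrence-only rate is truly intended, drop the word survival, name the population, and state how deaths without recurrence and never-resected patients are scored.

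The cost is a few lines of text. The sample size and visit schedule stay as they are. The downside is that the reported 1-year rate may be less favourable.

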Third, a few studies recently have explored neoadjuvant therapy of HCC. The final results of nivolumab alone or in combination with ipilimumab in the perioperative period of resectable HCC, a phase II randomized controlled, open-label study, were reported at the 2020 ASCO meeting. The results demonstrated that among 27 evaluable patients, the pCR rate was 19%, with 21 patients undergoing planned surgery (21). Another study in mildly resectable or locally advanced HCC reported at ASCO-GI 2021 showed that neoadjuvant therapy of cabozantinib combined with nivolumab achieved margin-negative resection in 12 of 15 patients, of which 5 were major/complete pathological response (22).

To date, there are no study on neoadjuvant therapy using lenvatinib and PD-1 inhibitor combined with radiotherapy for BCLC stage C. This study will provide preliminary evidence for the safety and efficacy of radiotherapy combined with lenvatinib plus PD-1 inhibitors (sintilimab) as neoadjuvant therapy for resectable HCC with PVTT. In addition, some interesting questions, such as the PVTT regression rate with neoadjuvant therapy and the consistency of imaging and pathological assessment of PVTT regression rates, will be explored in this study. In summary, this study may supplement the clinical decision-making evidence in the neoadjuvant treatment of BCLC stage C patients.

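### The imaging-pathology concordance rate is defined over all patients, though agreement can be assessed only in resected patients, so read literally it is capped at the resection share

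*Protocol article*

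**What the plan says.** The Outcome definitions section of the protocol article defines IPCR as "the proportion of all patients with consistent PVTT regression on preoperative imaging and postoperative pathological PVTT regression assessment". It does not restrict the denominator to operated patients and does not say how a patient without a specimen is counted.

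Three other places bear on this:

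- **Enrolment.** The Statistical analysis section states that "a planned 20 eligible subjects will be enrolled".
- **Surgery is an outcome.** Feasibility, part of the primary endpoint, is "the number of patients who complete pre-op treatment and proceed to surgery". In Table 4 (Follow-up section) the heading over the later visits covers all eligible patients and adds: "Non-operated patients will be counted from the day of neoadjuvant failure and surgical patients will be counted from the first postoperative day".
- **Purpose.** The Discussion lists "the consistency of imaging and pathological assessment of PVTT regression rates" among the questions the trial will explore. IPCR is the listed endpoint that answers it.

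**The concern.** Agreement between two assessments is defined only where both exist. A patient who does not reach surgery has no pathological reading, so imaging can neither agree nor disagree with it. Under the stated denominator that patient can never enter the numerator but still enlarges the denominator, which has the same effect as scoring a disagreement.

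The rate then mixes two different things: how well preoperative imaging reflects the pathology of the thrombus, and how many patients got to surgery. The second is already measured by the feasibility endpoint. A low IPCR could be read as a failing of imaging when it reflects non-resection. The Anticipated results section says that the trial's outcomes will be used to size a further study, so a misread rate could be carried forward.

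**Working it through.** **The plan's own figure.** The article gives no expected value, target or precision for IPCR, so there is none to reproduce. The enrolment of 20 follows from the calculated sample size of 18 and the 10% allowance for loss (18/0.9 = 20). That calculation does not concern IPCR.

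**Inputs.**
- N = 20 enrolled (Statistical analysis section).
- m = number resected. This is an outcome of the trial, at most 20. The documents do not predict it.
- k = number of resected patients in whom imaging and pathology agree. The documents give no value, so the agreement levels below are assumptions.
- For simplicity, every resected patient is taken to have an evaluable preoperative image.

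**Identity.** IPCR as written is k/N, which factors as

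k/N = (m/N) × (k/m),

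that is, resection share × agreement among resected patients. Since k/m cannot exceed 1, IPCR cannot exceed m/N.

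**Effect of the resection share, with agreement assumed to be 90%** (expected values, so k need not be a whole number):

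| Resected of 20 | m/N (ceiling) | IPCR as written | Agreement among resected |
|---|---|---|---|
| 20 | 100% | 1.00 × 0.90 = 90% | 90% |
| 18 | 90% | 0.90 × 0.90 = 81% | 90% |
| 16 | 80% | 0.80 × 0.90 = 72% | 90% |
| 14 | 70% | 0.70 × 0.90 = 63% | 90% |

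The quantity of interest is constant down the table. Everything that moves in the IPCR column comes from the resection share.

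**Same IPCR, different agreement.** Take k = 12 concordant patients, so that IPCR as written is 12/20 = 60%:

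- 20 resected: agreement 12/20 = 60%.
- 15 resected: agreement 12/15 = 80%.
- 12 resected: agreement 12/12 = 100%.

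One reported value fits both mediocre and perfect agreement.

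**The case against.** The strongest reply is that *all patients* is loose wording for all operated patients. The definition itself requires a postoperative assessment, and the 1-year recurrence-free definition in the same section uses the same words for an outcome timed from liver resection. This reading is possible, and under it the problem disappears. But nothing in the text says it. ORR, also in that section, is taken over all patients, and it is an imaging measure that needs no surgery. Two denominators therefore remain open, and the literal one misses the stated question. It is fair to add that the Table 4 heading describes visits and does not define an analysis set, and that no sentence says a patient without pathology is scored as discordant. That consequence follows from the literal denominator.

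A second reply is that the effect may be small. Eligibility requires a resectable primary tumor, and the five earlier patients described under Sample size all had surgery after the same regimen. They may have been selected for that, but if nearly all trial patients are resected the distortion is indeed near zero. IPCR is also one of several secondary endpoints in an exploratory trial, and a reader given k/N and the number resected could recover k/m. This limits the harm. It does not make the definition correct.

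A third reply is that keeping all enrolled patients in the denominator is conservative. That argument suits efficacy rates. For agreement between two readings there is no conservative value to impute when one reading does not exist.

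Four stronger readings might be inferred, and the documents do not support them:

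- **A ceiling of 80%.** The Discussion cites a study that "achieved margin-negative resection in 12 of 15 patients". That is a margin-negative count under another regimen and in another population, so it is not a forecast of the resection share here.
- **An invalid comparison of two regression rates.** The PVTT regression rate is "divided into PVTT regression rate assessed by imaging and PVTT regression rate assessed by pathology", but no direct comparison of the two is planned, and reporting them separately is not an error.
- **A numerator that counts only joint regression.** The wording leaves this open, but the endpoint's name and its stated purpose both point to agreement in general.
- **Missing diagnostic statistics.** A 2×2 table, sensitivity and specificity are reporting preferences. Their absence from a condensed article is not a fault.

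**Conclusion.** The point holds as a flaw in a stated definition, not as a complaint about missing detail. Read literally, IPCR is the resection share times the agreement among resected patients. It is capped at the resection share and cannot distinguish poor imaging agreement from failure to reach surgery.

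The identity needs no assumption about the size of either factor. The size of the distortion does: it is zero if all 20 are resected, and at an assumed 90% agreement it is 9, 18 or 27 percentage points with 18, 16 or 14 resected (90 − 81, 90 − 72, 90 − 63). The documents give neither the resection share nor the agreement to expect, so these figures show a range and do not predict the result.

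The definition should be corrected before analysis. The primary endpoint and the sample size are unaffected.

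**What to change.** Redefine IPCR in the Outcome definitions section:

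- **Numerator:** patients whose preoperative imaging and resection pathology agree on PVTT regression status, meaning both regressed or both not regressed.
- **Denominator:** patients with both an evaluable preoperative image and a resection specimen.
- **Report:** that denominator, with an exact 95% confidence interval for the rate. Describe the result as applying to resected patients.
- **Non-resection:** leave it to the feasibility endpoint, where it is already counted.

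The change is to wording only, with no new data or visits. The cost is a smaller denominator and a wider interval at the same observed proportion. For example, 90% observed as 18/20 has an exact (Clopper-Pearson) 95% interval of 68% to 99%, whereas 9/10 gives 55% to 99.7%.
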